## Abstract

**Background:**

More than 50% of the worldwide cases of hepatocellular carcinoma occur in China, and this malignancy currently represents the country's second leading cause of cancer death in cities and the leading cause in rural areas. Despite recent advances in the control and management of hepatocellular carcinoma within China, this disease remains a major health care issue. The global HCC BRIDGE study, designed to assess patterns of hepatocellular carcinoma therapy use and associated outcomes across real-world clinical practice, has recently been expanded as a national study in China, allowing a detailed analysis of hepatocellular carcinoma in this important country.

**Methods/Design:**

The global HCC BRIDGE study is a multiregional longitudinal cohort trial including patients newly diagnosed with hepatocellular carcinoma between January 1, 2005, and June 30, 2011, who are receiving treatment for hepatocellular carcinoma via sites in the Asia-Pacific, European, and North American regions. The HCC BRIDGE China national study comprises the portion of the global HCC BRIDGE study conducted within mainland China. Patients will be followed from time of diagnosis of hepatocellular carcinoma (post-January 1, 2005) to time of death or December 31, 2011, whichever comes first. Data will be collected on demographic/clinical characteristics, relevant laboratory values, hepatocellular carcinoma/underlying liver disease treatment, tumor response, adverse events, hospitalizations, and overall survival. The primary study end point is overall survival; secondary end points are disease progression, treatment-limiting adverse events, and treatment failure.

**Results:**

At the time of writing, 15 sites have selected for participation across all 7 traditional regions of China (North, North-East, East, South, South-West, North-West, and Central). The anticipated study population from the China national study is approximately 9000 patients.

**Discussion:**

Findings from the HCC BRIDGE China national study, the first geographically representative study of hepatocellular carcinoma in China, will contribute to the understanding of patterns of therapy use and related clinical outcomes and will provide further information on continuing unmet needs for hepatocellular carcinoma throughout this important country.

## Background

Hepatocellular carcinoma (HCC), one of the world's most prevalent and deadly malignancies [1,2], is particularly common in Asia-Pacific countries, with more than half of all cases occurring in China alone [2,3]. In most patients, HCC develops in association with liver cirrhosis and/or viral hepatitis infection. Indeed, the main risk factors for the development of HCC among the Chinese population are the presence of liver cirrhosis and chronic infection with hepatitis B virus [4]. Other risk factors include chronic hepatitis C virus infection, a family history of liver cancer, depression, ingestion of aflatoxin B1 via contaminated foodstuffs, and excessive alcohol consumption [4,5].

Current therapeutic options for HCC in China are varied, with treatment allocation generally dependent on the patient's liver function and tumor burden. Commonly used therapies include surgical techniques, such as liver resection and liver transplantation; interventional therapies, such as hepatic artery infusion and transcatheter arterial chemoembolization; and ablation techniques, such as anhydrous alcohol injection and radiofrequency or microwave ablation [6]. Systemic therapy options, including radiotherapy, immunotherapy, standard chemotherapy, and traditional Chinese herbal medicines, are also recommended [6]. In addition, the multikinase inhibitor sorafenib, which has demonstrated a reduction in death risk among advanced, inoperable HCC patients with mostly Child-Pugh A cirrhosis [7,8], is approved in China for treatment of advanced unresectable HCC.

In recent years, the China Ministry of Health has made great strides in the management of HCC by establishing it as one of 5 tumors of high national importance and by initiating a number of primary HCC prevention activities. These include providing government-funded HCC screening for persons in high-risk areas (within the Jiangsu and Guangxi provinces) who are positive for hepatitis B surface antigen and who have cirrhosis and, more recently, enacting mandatory hepatitis B virus vaccination programs. Despite these advances, HCC remains a cancer with a high mortality rate and a clear unmet medical need in China. Based on data from the Third China National Mortality Survey conducted in 2004/2005, HCC is the second leading cause of cancer mortality in cities and the leading cause in rural areas [9]. Moreover, this survey reported an HCC mortality rate in China of 26 deaths per 100,000 persons. When considering these mortality data, it is important to acknowledge that they are pooled from individual studies supported by the China Ministry of Health, and only represent certain regions of the country. As such, the reported national mortality rate may not accurately reflect the true burden of HCC across the country. Furthermore, given the lack of active surveillance, there remain many unanswered questions surrounding the epidemiology and management of HCC in China.

The global HCC BRIDGE study is an ongoing longitudinal cohort trial of patients with HCC in 3 core geographic regions (Asia-Pacific, European, and North American) that is designed to (1) evaluate current treatment approaches to HCC and associated clinical outcomes, and (2) determine the real-world impact on clinical outcomes of new HCC treatments, such as sorafenib, versus other therapies [10]. Recently, the HCC BRIDGE study was expanded as a national study in China allowing a specific and more detailed evaluation of HCC across this important country.

## Methods

### Study design

The global HCC BRIDGE study is a multiregional longitudinal cohort trial including patients diagnosed with HCC from January 1, 2005, to June 30, 2011 [10]. Patients enrolled in the study will be followed from the date of HCC diagnosis to December 31, 2011, or date of death, whichever comes first. The HCC BRIDGE China national study comprises the portion of the global HCC BRIDGE study conducted within mainland China. To ensure that the national study is geographically representative, it was designed to include patients enrolled at sites from all 7 traditional regions across China (North, North-East, East, South, South-West, North-West, and Central).

### Study sites

Sites have been selected for inclusion in the China national study on the basis that (1) they are tertiary care centers providing surgical and routine follow-up care for patients with HCC or are oncology centers that care for these patients; (2) the type and proportion of etiologies for HCC are consistent with the Chinese national average; and (3) the HCC screening practices, when used, are in accordance with Chinese national standards. In addition, sites may be selected if the patient population was, on a prior occasion, used to characterize the Chinese national HCC population for other research purposes, for example during evaluation of national HCC incidence/prevalence rates or the establishment of national HCC staging systems.

### Patients

All patients enrolled in the HCC BRIDGE study must meet 3 key inclusion criteria: (1) diagnosed with HCC between January 1, 2005, and June 30, 2011, in accordance with American Association for the Study of Liver Diseases/European Association for the Study of the Liver guidelines [11]; (2) aged at least 18 years at the time of HCC diagnosis; and (3) received or receiving treatment for HCC through a site enrolled in the HCC BRIDGE trial. Patients participating in other clinical trials will be included in the study if the patient is enrolled in a single-arm clinical trial, enrolled in a randomized clinical trial of HCC adjuvant therapy, or was not selected to receive active treatment in a randomized clinical trial that was conducted between 2005 and 2007. Any patient whose first active HCC-directed treatment is received via participation in a randomized clinical trial of primary HCC therapy will be excluded from the current study, since this treatment regimen would have been determined by a study protocol rather than by the treating physician. Similarly, patients included in the China national study who subsequently enroll in such a trial will be censored from the study at that time point. Patients with unknown month and year of HCC diagnosis or of the first visit at the site of inclusion will be excluded. Furthermore, to preserve regional representation within China, patients who reside outside the province of interest for a particular study site will also be excluded. Finally, in order to avoid selection bias when the number of eligible patients at a site exceeds the number allowed according to study sample size calculations, an enrollment scheme will be adopted such that the same number of consecutive patients are enrolled each month. For example, in the first year of data entry, if a site is to enroll 200 patients, approximately 17 consecutive patients diagnosed with HCC will be enrolled in each month. If there are less than the specified numbers of patients in any given month, we ask that the corresponding number of extra patients be enrolled in the following month.

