### Data analysis

To evaluate therapeutic approaches to HCC in China, the number and percentage of patients using each treatment (plus any new treatments that are approved and used within the study period) will be determined for each study year, in total and stratified by disease stage and site. Treatment patterns will also be assessed by disease stage for each study year. Patient characteristics will be stratified by disease stage and by site for each study year.

To assess therapeutic outcomes, age- and gender-adjusted rates will be calculated for each study end point. Cox proportional hazard models will be used for the time-to-event end points (overall survival and disease progression) to determine hazard ratios for each treatment approach, and Kaplan-Meier curves will be generated. Logistic regression models will be used for categorical end points (treatment-limiting adverse events and treatment failure). Covariates for the models will include disease stage, gender, age, duration of disease, etiology of disease, liver status, tumor size/spread, surgical intervention/number of interventions, and number of comorbidities; analyses will be conducted at the site and country level. The same analysis plan will be adopted for the evaluation of survival and other clinical end points with sorafenib versus other therapies, except that "treatment" will be included as a covariate. Further analyses will be conducted to evaluate clinical characteristics and demographics of patients treated with sorafenib versus other treatments for HCC. In addition, data collected will be used to analyze additional aspects related to HCC epidemiology and management in China (Table 2). All tests of statistical significance will be carried out at the 0.05 level.

**Table 2 T2:** Additional aspects of HCC management for potential evaluation using data from the HCC BRIDGE China national study.

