The eventual findings of the HCC BRIDGE China national study will need to be considered in light of the study's strengths and weaknesses. The primary strengths of this study are (1) the large number of patients included; (2) the geographic representativeness of the included sites; and (3) the use of real-life clinical practice data. Additional strengths include the use of centralized data monitoring, cleaning, site queries, and checking of invalid clinical values, which will enhance the quality of the collected data, as well as the use of identified prognostic factors for HCC survival to control for population differences that may influence treatment outcomes. The main potential study limitations are (1) treatment comparisons are performed in patients without prospective randomization methodology; (2) both academic and nonacademic centers/hospitals are included, which may result in differing quality of medical care for enrolled patients; (3) data quality is dependent on the thoroughness of the clinician's documentation of medical history, treatment, and outcomes; and (4) data collection bias is possible since clinical assessments are not conducted at predefined time points, as in a clinical trial, but at times determined by clinicians and their patients.

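### Single-arm trial patients are kept although the printed reason for excluding other trial patients applies to them equally, so protocol-assigned treatment enters results presented as real-life practice

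*Protocol article*

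**What the plan says.** All the eligibility rules on trial participants stand in one paragraph of the protocol article (Methods, Patients).

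- **Kept, single-arm trials:** "Patients participating in other clinical trials will be included in the study if the patient is enrolled in a single-arm clinical trial". No limit on agent, line of therapy or calendar period is given.
- **Kept, adjuvant trials:** patients "enrolled in a randomized clinical trial of HCC adjuvant therapy".
- **Kept, non-active patients:** a patient who "was not selected to receive active treatment in a randomized clinical trial that was conducted between 2005 and 2007".
- **Excluded:** "Any patient whose first active HCC-directed treatment is received via participation in a randomized clinical trial of primary HCC therapy will be excluded".
- **Reason given for the exclusion:** "since this treatment regimen would have been determined by a study protocol rather than by the treating physician".
- **Later entry:** "patients included in the China national study who subsequently enroll in such a trial will be censored from the study at that time point". This refers to randomized trials of primary therapy only.

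The Data analysis section plans to report "the number and percentage of patients using each treatment" for each study year, in total and by stage and site. It also plans Cox models with a hazard ratio per treatment approach, and the same analysis for sorafenib against other therapies. The Comparator groups section defines sorafenib treatment by use of the drug, alone or close in time to other treatment, without regard to whether a trial supplied it. The Discussion lists "the use of real-life clinical practice data" among the primary strengths.

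**The concern.** The paragraph gives one principle for leaving trial patients out: their treatment was set by a protocol. It then keeps a group in which that is true of every member. A single-arm trial gives each participant the protocol regimen.

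Three planned results are exposed:

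- **Treatment patterns.** Use under a single-arm protocol is tabulated together with use in ordinary care. A site could appear to differ in practice because of its trial portfolio, and the results are to be shown by site and year.
- **Treatment hazard ratios.** Trial participants may differ from other patients in ways the listed covariates do not capture. Trial participation is not among those covariates.
- **The sorafenib comparison.** If a retained single-arm trial gave sorafenib, its patients would count as sorafenib-treated. Matching to historic controls is on age, sex, Child-Pugh status and stage, none of which records trial entry. The availability periods are separated by the first recorded sorafenib use at each site, so such a patient could also set a site's boundary.

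The limitations listed in the Discussion do not mention retained trial patients, so a reader would take the results as routine care throughout.

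**Working it through.** No stated figure is in dispute, so there is none to reproduce. The check is a comparison of each rule with the printed reason, followed by arithmetic for scale.

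**Step 1. Apply the reason to each trial type.**

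| Trial type | Is the first active treatment set by a protocol? | Is later treatment set by a protocol? | Rule |
|---|---|---|---|
| Randomized, primary therapy | Yes, if it is the first treatment | Yes, if entered later | Excluded, or censored at entry |
| Single-arm | Yes, if it is the first treatment | Yes, if entered later | Kept, no censoring stated |
| Randomized, adjuvant | No, primary treatment comes first | Adjuvant component only | Kept |

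The first two rows get the same answers and opposite rules. The third differs in its first answer, so keeping adjuvant patients fits an exclusion worded around the first active treatment. Only the adjuvant component (or its absence) is protocol-assigned there. The non-active patients kept for 2005 to 2007 are a separate matter and are not relied on here.

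**Step 2. Follow a single-arm patient through the analysis as written.** The patient is eligible, is counted under the trial agent for the year and site, and contributes survival time to that treatment's hazard ratio. If the agent is sorafenib, the patient also joins the sorafenib group. Nothing printed in the article separates this treatment from ordinary use.

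**Step 3. Scale, on assumed counts.** From the document: about 200 patients per site per year for 2008 to 2010 (Sample size), and 15 sites and about 9000 patients in all (Results). Assumed: one single-arm trial contributes 20 to 40 patients in a site-year.

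- Share of one site-year: 20/200 = 10%; 40/200 = 20%.
- Pooled year if all sites meet target: 15 × 200 = 3000. Then 20/3000 = 0.7% and 40/3000 = 1.3%. Three such years give 3 × 3000 = 9000, which alone uses up the whole anticipated population, so the true pooled yearly denominator may be smaller and these shares larger.
- Study-wide, for assumed shares of 1%, 5% and 10%: 0.01 × 9000 = 90; 0.05 × 9000 = 450; 0.10 × 9000 = 900 patients.

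**Step 4. Why the denominator must be stated.** Let f be the share of patients treated by the trial and p the agent's use among the rest. With everyone counted, the reported use is f + (1 − f)p.

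- Drop the trial treatments but keep the patients in the denominator: use is (1 − f)p, a change of f.
- Drop the patients as well: use is p, a change of f(1 − p).

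The two restricted figures differ whenever f and p are both above zero.

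**The case against.** **Randomization is the real criterion.** Every exclusion and censoring clause is limited to randomized trials. Randomization takes the choice between treatments away from the physician, whereas in a single-arm trial physician and patient opt for a known treatment. Excluding such patients would also select people out of the consecutive enrollment scheme. This is a reasonable design position, and it makes outright exclusion debatable. It does not rescue the text, because the reason printed is that a protocol set the regimen, not that allocation was random.

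**The table only counts use.** The Data analysis section does not say that each use was chosen by a physician. That is right, but the study presents its data as real-life practice, and its own exclusion treats protocol-set treatment as outside that description.

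**The models adjust.** Stage, liver status, tumor size and spread, and number of comorbidities are covariates, so part of any selection on fitness is addressed. This stands in part: it does nothing for the treatment percentages, and adjustment does not make trial care into routine care.

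**A flag or sensitivity analysis belongs in the full protocol or analysis plan.** Agreed. Its absence from the article is not held against the plan. The inconsistency lies in the printed rule and reason.

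**Conclusion.** The point holds for single-arm trials. The exclusion reason and the single-arm inclusion conflict as printed, and under the stated rules protocol-assigned treatment enters the treatment percentages and the treatment and sorafenib hazard ratios. It is worth correcting because it bears on the real-life claim and the correction is cheap.

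Four stronger readings are tempting, and the document does not support them:

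- **That adjuvant trials are an equal contradiction.** Primary treatment there precedes the trial and is physician-chosen. Only the adjuvant component is affected.
- **That survival is biased upward, or that use is inflated by a known amount.** Neither the number of such patients nor the direction of bias can be derived. Single-arm trials may take fitter patients, or patients with few options left.
- **That patients in blinded adjuvant trials cannot be classified.** The document mentions no blinded trial.
- **That single-arm patients must be removed from the cohort.** The conflict can be resolved in the analysis without changing enrollment.

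The 10% to 20% site-year shares rest wholly on the assumed 20 to 40 patients. On the same assumption one such trial is only 0.7% to 1.3% of a full pooled year, so the concern weighs more on site-level than on country-level results.

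**What to change.** 1. **Flag** each treatment assigned by an interventional trial, with the trial type (single-arm, or randomized adjuvant). Sites already need this information to apply the eligibility rule.
2. **Report twice.** Give the treatment-use percentages and the treatment and sorafenib hazard ratios with and without trial-assigned treatments.
3. **Define the restricted version.** State the denominator of the percentages. Keep treatment given before trial entry, such as the primary treatment preceding an adjuvant trial, and censor follow-up at trial entry, as is already done for randomized trials of primary therapy. Survival is counted from treatment initiation, so a patient whose first active treatment is the trial regimen contributes no follow-up to the restricted models.
4. **Reconcile the Patients section.** Either say that randomization is the criterion and why single-arm patients are kept, or apply the protocol-set reason to all trial-assigned treatment. Add retained trial patients to the limitations.

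**Cost:** one flag, one extra analysis, and somewhat fewer patients in the restricted version, more noticeably at a site with many trial patients. Censoring at trial entry may be informative, since patients who enter trials may differ in prognosis, so the two versions should be read together. Enrollment does not change.

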### Comparator groups

In order to evaluate the influence of sorafenib on HCC treatment patterns in China, clinical outcomes will be compared across 2 periods within the overall study duration: (1) the period when sorafenib was unavailable (2005 to 2007) and (2) the period when sorafenib was available for use (2008 to 2011). These 2 periods will be differentiated by the first record of sorafenib use at each site. Patients treated during the period when sorafenib was not available will act as historic controls and will be statistically matched within the pool of patient data by age, sex, Child-Pugh status, and HCC stage to patients treated with sorafenib between 2008 and 2011. Patients treated with non-sorafenib therapies during the period when sorafenib was available will act as concurrent controls and will be used to evaluate characteristics of HCC patients treated with sorafenib versus other therapies. In this study, "sorafenib treatment" is defined as the use of either sorafenib alone or concomitant use of sorafenib and other pharmacologic agents or interventions within 21 days of each other.

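### The matched comparison of sorafenib patients with pre-sorafenib historic controls does not control for calendar time, so it confounds the drug with changes in care that the matching and covariates do not capture

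*Protocol article*

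**What the plan says.** The Comparator groups section sets out the sorafenib evaluation.

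- **Contrast.** To evaluate sorafenib's influence, "clinical outcomes will be compared across 2 periods within the overall study duration": 2005 to 2007 (unavailable) and 2008 to 2011 (available).
- **Boundary.** "These 2 periods will be differentiated by the first record of sorafenib use at each site".
- **Historic controls.** Patients from the earlier period are "statistically matched within the pool of patient data by age, sex, Child-Pugh status, and HCC stage" to patients given sorafenib in 2008 to 2011.
- **Concurrent controls.** Patients given other therapies in the later period "will act as concurrent controls and will be used to evaluate characteristics of HCC patients treated with sorafenib versus other therapies". Outcomes are not named as a use.

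The Data analysis section gives the models. "Covariates for the models will include disease stage, gender, age, duration of disease, etiology of disease, liver status, tumor size/spread", followed by surgical intervention or number of interventions and number of comorbidities. The same plan covers "evaluation of survival and other clinical end points with sorafenib versus other therapies, except that 'treatment' will be included as a covariate". The period of the comparator in that model is not stated. A comparison of patient characteristics is then listed as a further analysis. "All tests of statistical significance will be carried out at the 0.05 level".

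The Discussion names four main limitations. Lack of randomisation comes first; change over calendar time is not among them.

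**The concern.** Within a site, every historic control predates the first recorded sorafenib use, and every sorafenib patient follows it. Drug and era therefore move together. Matching on four patient factors balances case mix, including stage. It does not balance anything else that changed in the care of same-stage patients between the two periods, such as supportive or locoregional care.

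The Background gives as an aim of the global study, of which this is the China portion, to determine the real-world effect of new treatments such as sorafenib on outcomes. Overall survival is the primary end point. If survival improved for other reasons, the matched contrast would estimate sorafenib plus that improvement and could be significant at 0.05 when the drug does nothing. More patients would not help, because the estimate would settle more tightly on the combined effect.

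**Working it through.** **1. Is calendar time controlled anywhere in the sorafenib comparisons?**

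| Element | Stated content | Calendar time? |
|---|---|---|
| Matching of historic controls | age, sex, Child-Pugh status, HCC stage | no |
| Model covariates | patient, disease and intervention factors | no |
| Sorafenib outcome model | same plan, with treatment added | no; comparator period not stated |
| Concurrent controls | patient characteristics | would share the period, but outcomes are not named |
| Tabulation by study year | treatment use and patient characteristics | descriptive only |
| Main limitations | four items | not named |

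The article gives no effect size, event count or power for this comparison, so there is no stated figure to reproduce. The rest is illustration.

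**2. Time gap between the groups.** The Sample size section gives about 200 patients per site per year for 2008 to 2010, about 192 for the first half of 2011, and 100 per site for 2005 to 2007. With even enrolment within each interval (assumed):

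- late-period mean = 2008 + [200 × (0.5 + 1.5 + 2.5) + 192 × 3.25] / 792 = 2008 + 1524/792 = 2009.92
- early-period mean = 2006.5
- gap = 3.42 years

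This averages all late-period patients. Sorafenib patients alone could have a different mean date.

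**3. Hazard ratio with no drug effect.** If the mortality hazard falls by a fraction d per year for other reasons (assumed range), HR = (1 − d)^3.42:

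- d = 1%: 0.97
- d = 3%: 0.90
- d = 5%: 0.84

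**4. Chance of a significant result with no drug effect.** Assume n matched pairs, 93% of controls and 65% of sorafenib patients dead at analysis, and a two-sided test (sidedness is not stated). SE(log HR) = √[1/(0.93n) + 1/(0.65n)], and z = |3.42 × ln(1 − d)| / SE. The chance is Φ(z − 1.96) + Φ(−z − 1.96).

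| d per year | 200 pairs | 500 pairs | 1500 pairs |
|---|---|---|---|
| 1% | 0.06 | 0.08 | 0.13 |
| 3% | 0.15 | 0.30 | 0.70 |
| 5% | 0.34 | 0.68 | 0.99 |

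For d = 3% and n = 500: SE = 0.072, z = 1.44, chance 0.30. The 1500 column is a ceiling: 100 controls × 15 sites, all matched. The Background says sorafenib is approved for advanced unresectable disease, so matching on stage would leave far fewer usable controls.

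A separate calculation by events, with SE = √(4/events), points the same way: at a background HR of 0.90, the chance is 22%, 38% and 65% with 500, 1000 and 2000 events.

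**5. Could a calendar term separate era from availability?** Enrolment was simulated at 15 sites with the stated quotas, and the variance inflation of the period indicator was computed given site and calendar-year indicators.

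- All sites switching on 1 January 2008: infinite, because period is fully collinear with year. A linear trend term gives about 2.1 (100 historic controls per site) or 3.3 (300 per site, if the 100 is read as yearly), but rests on linearity.
- First-use dates spread over 1 to 3 years (assumed): about 3.2 to 5.4.

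So a calendar term helps only if the first-use dates differ enough, and then at a cost in precision.

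**The case against.** **A concurrent survival comparison may already be planned.** The Data analysis section plans a survival model of sorafenib versus other therapies, separately from the comparison of characteristics, and nothing excludes concurrent patients from it. This stands. A reader might infer that sorafenib is judged only by the before/after contrast, or that concurrent patients may be used only for characteristics; the text does not support either. But the comparator of that model is not named, and a concurrent comparison would bring confounding by indication without repairing the matched historic one.

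**The site-specific boundary may separate era from drug.** A reader might infer that sites switched at different dates. The article states the rule but gives no dates, and describes a single split at 2007/2008.

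**The evidence of a changing era is thin.** The Background says "In recent years, the China Ministry of Health has made great strides in the management of HCC", but then describes prevention: screening in high-risk areas of two provinces, and hepatitis B vaccination. Screening acts largely through earlier stage, which is matched and adjusted for; vaccination bears on incidence. This stands in large part. The passage makes a period difference plausible but documents no change in care after diagnosis for patients of the same stage. It is therefore too strong to say that any improvement in care would be credited to sorafenib; only what the matching and covariates miss would be.

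**This is a condensed article.** The covariate list need not be exhaustive, a calendar term may sit in an analysis plan not shown, the earlier patients are openly called historic controls, and lack of randomisation is acknowledged. This lowers the severity. It does not remove the point, because the article itself fixes the contrast, the four matching factors and the stated role of each control group.

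**Conclusion.** The point holds in a limited form and should be fixed. Followed as written, the matched contrast of sorafenib patients with historic controls combines the drug with any change in care between the periods that is not captured by the matching factors or the listed covariates. The limitations do not say so, and the comparator period of the sorafenib survival model is left open.

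The confounding follows from the design and needs no assumption, but its size is unknown. The hazard ratios of 0.97 to 0.84 and the false-positive chances rest on assumed trends, death proportions and pair counts; at 1% per year with a few hundred pairs, the distortion is small. A reader might conclude that the sorafenib results will be invalid or that the bias is large. The documents support neither: they give no secular trend, and a concurrent survival analysis may already be intended.

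**What to change.** 1. State that the matched period contrast combines sorafenib with era, do not attribute it to sorafenib alone, and add secular trend to the limitations.
2. With the same models, estimate the before/after change in outcome among patients in stages where sorafenib is little used. Report it beside the sorafenib contrast as a check on background trend. Taking all later-period non-sorafenib patients instead is less clean, because they are those left after selection for sorafenib.
3. Name the comparator in the sorafenib outcome model. Run it against concurrent non-sorafenib patients as a separate analysis, and state that confounding by indication remains.
4. Tabulate each site's first-use date. Add a calendar-time term only if the dates are spread enough; with a common date, calendar-year indicators are collinear with period.

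The cost is wording and a few further models on data already planned for collection. The downsides are wider intervals, an assumption of similar trends across stages in item 2, and residual confounding by indication in item 3.
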